### Aims

This study aims to investigate the effect of prednisolone augmentation to antipsychotic pharmacotherapy in patients with a psychotic disorder. The primary objective of this study will be the change in symptom severity (PANSS) between baseline and end-of-treatment (6 weeks treatment). Secondary objectives include changes in symptom severity in the follow-up phase, cognition, depressive symptoms, global functioning, prediction of treatment response to prednisolone therapy using immune markers (blood samples), and insight into psychosis and inflammation in the brain using magnetic resonance imaging (MRI).

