#### Stopping rules

Several events that may jeopardize the patient’s health will prompt clinicians to end the study and start tapering the patient off the study medication immediately in line with the treatment guidelines for inflammatory bowel diseases (2008). These events include the patient developing:
A (fasting) blood glucose exceeding 7.0 mmol/L; in case a non-fasting glucose level was determined, a blood glucose level exceeding 11 mmol/LSuicidal ideations assessed by the CDS, the following cut-off are applicable based on item 8: Suicidal ideations within the CDS
◦ Score of 0: no action (no suicidal ideation)◦ Score of 1: consult with clinician (passive suicidal ideation)◦ Score of 2/3: potential cause to stop study medication treatment—consult with clinician (active suicidal ideation)A PANSS positive subscore which increases by 10 or more points without a clear reason (i.e., medication non-adherence)PANSS item G6 (depression) exceeding a score of 4The need for coercive treatmentPregnancyOral systematic infectious disease

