### Power calculation and statistical analysis

A two group *t*-test with a 0.050 two-sided significance level will have 80% power to detect an effect size of 0.610 when the sample sizes in the two groups are 44 and 44, respectively (a total sample size of 88; text generated by nQuery Advisor). Subsequently, the sample size can be reduced by the data with an Ancova instead of analyzing a *t*-test [46]. The level of reduction depends on the correlation (r) between baseline and follow up measurements: N-ANCOVA = ((1 − r2) × N *t*-test) + 1. From a previous study in this hospital (OPTiMiSE trial) where a PANSS was performed at baseline and after 6 weeks, r = 0.48 was found. Therefore, N-ANCOVA = ((1 − 0.482) × 88) + 1 = 68.7248. Lastly, we expect a considerable number of drop outs. Assuming a drop-out rate of 30%, the definitive sample size is calculated at 68.7248 × 1.3 = 89.34224, which makes a total of *N* = 90 patients.

Statistical analyses for baseline characteristics and the outcomes regarding symptom severity, global functioning, depressive symptoms, and cognition will be performed in IBM SPSS Statistics version 25.0 [47]. A summary of the baseline characteristics will be created in order to assess baseline differences across the treatment groups. Normal distributed data will be expressed as means and standard deviations, and categorical data will be expressed as percentages. The baseline characteristics of the prednisolone and placebo group will be compared and tested with a *t*-test (for continuous variables) and a Chi-square test (for categorical variables). In this study we will use a mixed model analysis. Since we do not estimate a linear change in this analysis, the increase in efficiency compared to the analysis of covariance and therefore the reduction in sample size will not be immense and this calculation will suffice. The mixed model analysis will allow us to use the data of the discontinued patients as it takes into account all observations. This analysis will be used for the objectives regarding symptom severity, global functioning, depressive symptoms, cognition, and MRI. As stratification was performed for gender, center, and country, these variables will be used as covariates in the analyses in addition to variables that are significantly different between treatment groups as well as the unused pills (percentage over the whole treatment period) to take into account compliance with study medication.

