Statistical analysis for the prediction of treatment response to prednisolone therapy using immune markers will be conducted using R software. Protein concentrations before and after treatment with prednisolone and placebo will be compared using mixed effects analysis of covariance adjusted for covariates significantly differing between the groups. Association of clinical outcomes with baseline levels of selected biomarkers in the prednisolone treatment group (i.e., prediction of treatment response) will be assessed using fixed effects analysis of covariance with adjustment for significant covariates. Sensitivity analyses will be conducted by excluding covariates from the analysis of covariance models and, if applicable, including outliers.

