#### Treatment visits

After the baseline visit, patients will be assessed weekly for 6 weeks. During various visits, a trained study team member will interview them using the PANSS, GAF (every other week; visits 2, 4, 6, and 8) and CDS questionnaires (weekly). At each visit, the presence of suicidal ideation is carefully monitored. Co-medication use will be noted as well as side effects and treatment compliance. Except for visit 8, study medication will be dispensed during each visit during the treatment period. Alcohol and drug use will be assessed using the alcohol/drug use section of the CASH during visits 5 and 8 in the Netherlands and Belgium, whereas similar forms will be used in Norway. At visits 2, 5, and 8 blood draws intended for immunological assessments will be performed. After the blood draw the patients need to remain within the hospital (when possible) until the laboratory values are checked by a physician in case follow-up treatment is necessary. Furthermore, pill boxes are returned to the study centers each week to assess compliance with study medication. Cognitive testing will take place at the end (6 weeks) of the treatment period.

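### The primary PANSS model adjusts for the percentage of unused pills, a post-randomisation variable, which leaves the treatment estimate open to bias of unknown size and direction

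*Protocol article*

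**What the plan says.** Under Power calculation and statistical analysis, the protocol article plans a mixed model and fixes its covariates: the stratification factors (gender, center, country), variables that differ significantly between arms, "as well as the unused pills (percentage over the whole treatment period) to take into account compliance with study medication". On scope, the same section says: "This analysis will be used for the objectives regarding symptom severity, global functioning, depressive symptoms, cognition, and MRI". Symptom severity includes the primary outcome, PANSS total from baseline to week 6 (Aims; Primary outcome variables).

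Three other parts of the article bear on this covariate:

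- **When it is measured.** Under Treatment visits, "pill boxes are returned to the study centers each week to assess compliance with study medication", so the count builds up after randomisation.
- **How treatment can change it.** Stopping rules lists "blood glucose exceeding 7.0 mmol/L" among the events that end study medication, and Patient withdrawal lists intolerance.
- **How the outcome can change it.** Stopping rules also lists a "PANSS positive subscore which increases by 10 or more points without a clear reason", and PANSS item G6 above 4. Both are components of the PANSS total.

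The one sensitivity analysis that drops covariates reads "Sensitivity analyses will be conducted by excluding covariates from the analysis of covariance models and, if applicable, including outliers". It stands in the paragraph on immune markers and concerns those models, not the PANSS mixed model.

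**The concern.** Randomisation balances what exists at baseline. It does not balance a variable that develops afterwards and can respond to the drug and to the course of illness. Conditioning on such a variable does two things. It removes any part of the treatment effect that runs through adherence. It also compares patients who reached the same pill count for different reasons, for example drug side effects in one arm and a worse course of illness in the other.

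The stated purpose is to take account of compliance, but the adjustment does not achieve it. The coefficient is neither the effect in all patients as allocated nor the effect in those who would take the drug. If prednisolone patients leave more pills and patients with more unused pills do worse, adjustment makes prednisolone look better than it is. If benefit improves adherence, part of a real effect is removed. The primary test is at stake, and the same covariate list applies to the other outcomes analysed with this model.

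**Working it through.** **1. The plan's own figure.** A two-sample t-test with 44 per arm, effect size 0.61 and two-sided alpha 0.05 has 80.8% power, and 44 is the smallest group size that reaches 80%. Then (1 - 0.48²) × 88 + 1 = 68.7248, and 68.7248 × 1.3 = 89.34, rounded up to 90. The stated total is reproduced. Unused pills do not enter this calculation.

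**2. Formula.** For an ANCOVA of week-6 PANSS with baseline as covariate, adding unused pills shifts the treatment coefficient by

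bias = -(slope of outcome on unused pills within arm) × (arm difference in unused pills).

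With outcome SD 1 and baseline correlation 0.48 (the article's r), the residual SD is √(1 - 0.48²) = 0.877. With unused pills scaled to SD 1 within arm, the slope is the within-arm correlation × 0.877. A negative value favours prednisolone.

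**3. Illustration with no true effect.** The number analysed is 64: 90 less 30% is 63, made even. The correlations and arm differences are assumptions, because the documents give no compliance data.

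| Correlation | Arm difference (SD) | Bias by formula (SD) | Simulated type I error |
|---|---|---|---|
| 0.2 | 0.25 | -0.2 × 0.877 × 0.25 = -0.04 | about 5% |
| 0.3 | 0.50 | -0.3 × 0.877 × 0.50 = -0.13 | 9% to 10% |
| 0.4 | 0.75 | -0.4 × 0.877 × 0.75 = -0.26 | 22% |

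Simulation agreed with the formula. Without the covariate, bias was about 0 and type I error about 5%. The middle row is 0.13 / 0.61, about 22% of the design effect.

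**4. A second set-up that keeps all 90 patients** (45 per arm, again ANCOVA). In the first four rows, an unmeasured prognostic factor is related 0.5 to both unused pills and PANSS.

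| True effect (SD) | Assumed path | Estimate with unused pills in the model (SD) |
|---|---|---|
| 0 | treatment raises unused pills by 0.3 / 0.5 / 0.8 SD | -0.07 / -0.12 / -0.20 (type I error 6% / 10.5% / 18%) |
| -0.61 | treatment raises unused pills by 0.5 SD | -0.73 |
| -0.61 | treatment lowers unused pills by 0.3 SD | -0.54 |
| 0 | treatment does not change unused pills | 0.00 |
| -0.61 | PANSS drives unused pills (0.3 / 0.5), no direct treatment path | -0.57 / -0.49 |
| 0 | treatment raises unused pills by 0.5 SD, pills unrelated to PANSS | 0.00 |

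The shift can go either way, and it is zero in the two cases where one of the links is missing.

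**5. Dependence on model form.** The article does not say whether baseline PANSS is a covariate or one of the repeated outcomes. In the second form, with a treatment-by-visit effect, a covariate that is constant over time and enters only as a main effect drops out of each patient's change from baseline. This was simulated with 90 patients, visits at weeks 0, 2, 4 and 6, no true effect, correlation 0.3 and arms 0.5 SD apart. The week-6 change contrast was +0.006 SD (type I error 3.9%). With dropout depending on unused pills it was -0.016 SD (5.6%), the same estimate as without the covariate. The bias of about -0.13 SD appeared when baseline was a covariate or when unused pills interacted with visit.

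**The case against.** The strongest reply is that nothing in the documents shows the estimate to be biased. This stands. There are no compliance figures, the bias is zero in plausible limiting cases, and under the repeated-baseline form it largely cancels. The sample-size section reasons from ANCOVA, which makes the baseline-as-covariate form plausible, but the article does not commit to it.

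A reader might also infer that a patient who worsens gets a high unused percentage by rule. The documents do not support that. The PANSS positive rule exempts rises with a clear reason such as non-adherence, stopping involves tapering, and the article does not say whether pills never dispensed count as unused. The path from outcome to pill count is open, not automatic. The G6 rule carries no such exemption.

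The 64-patient illustration leaves out discontinued patients, whom the mixed model is meant to keep. The second set-up keeps all 90 and gives shifts of similar order, but it too uses a single endpoint.

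Finally, this is a proof-of-concept trial reported in a condensed article, and a full protocol or SAP may hold a PANSS analysis without this covariate. The proof-of-concept aim explains the interest in drug actually taken, but it does not make this adjustment a valid way to study it. The covariate is also not a detail left to another document: the article states it outright.

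**Conclusion.** The point holds in a limited form. The article puts a post-randomisation variable, which its own stopping and withdrawal rules link to both treatment and PANSS, into the model for the primary comparison. The resulting coefficient need not estimate the randomised effect, is not a complier effect, and is open to bias of unknown size in either direction. Under an ANCOVA form with no true effect and the assumptions in the first table, the bias runs from about -0.04 to -0.26 SD and type I error from about 5% to 22%. These figures illustrate; they do not predict. A reader might infer that the estimate is certainly biased, that it favours prednisolone, or that the 5% level is certainly lost. The documents do not support any of these, since each depends on adherence data and a model form that they do not give. That the covariate is unsuitable for a randomised comparison depends on none of the simulated numbers.

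**What to change.** Delete unused pills from the covariate list of all randomised comparisons: PANSS, GAF, CDS, cognition and MRI. Keep the stratification factors and analyse all randomised patients as allocated. If adherence is of interest, address it only in a separate analysis labelled supportive, for example a complier analysis with randomisation as the instrument and drug actually taken as the exposure. The cost is one sentence in the protocol or SAP. No new data are needed, and N = 90 does not change. Trial status reports Norwegian recruitment as still open, so at that date the change could be made before the final analysis.

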Fourth, immune dysregulation in psychotic disorder patients might be reflected by abnormal levels of cytokines and the presence of auto-antibodies in serum and cerebrospinal fluid (CSF) [18]. A recent meta-analysis reported significant increase in interleukin (IL)-6 and IL-8, cytokines involved in inflammatory reactions, in schizophrenia patients compared to healthy controls [19]. A recent study found that symptom severity measured with the Positive and Negative Syndrome Scale (PANSS) [20] was strongly correlated with cytokine levels in the blood that are involved in inflammation [21]. It was found that symptom severity was positively associated with the levels of pro-inflammatory markers such as IL-2R, IL-6, and IL-8. Additionally, a large longitudinal study performed in Finland found an association between high-level C-reactive protein (CRP) values and the development of schizophrenia [22]. Associations between CRP levels and cognition in schizophrenia patients have also been described in a recent systematic review [23]; higher CRP levels (> 3 mg/L) were associated with declined cognitive performance (general intellectual ability, abstract reasoning, working memory, semantic memory, learning abilities, attention, mental flexibility, and processing speed).

Altogether, there is accumulating evidence on the presence of immune dysregulation in patients with schizophrenia, justifying the research into augmenting antipsychotic therapies with anti-inflammatory agents. However, at this stage it is unclear whether an increased pro-inflammatory status is characteristic for all patients with schizophrenia; instead it might be applicable to a specific subset of schizophrenia patients. This aligns with the findings of Schwarz and colleagues, who studied molecular abnormalities in patients with schizophrenia through multiplex immunoassay analyses and were able to distinguish two subgroups based on predominant abnormalities in immune molecules or growth factors and hormones [24].

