##### Laboratory assessments

Immunological and metabolic parameters will be assessed four times over the 1-year study period. We will investigate inflammatory processes that may be involved in a subpopulation of patients with psychotic disorders using prednisolone augmentation [33]. To investigate immunological biomarkers that predict treatment response to prednisolone therapy, we will collect serum and RNA of all patients at baseline and 3, 6, and 26 weeks after the start of the study medication use. The laboratory assessments will contain the following analyses:
Multiplex immunoassayInfectious disease profilingFlow cytometrySelective reaction monitoring (SRM)

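### Prediction of response to prednisolone is tested within the prednisolone arm only, so a merely prognostic marker can be reported as a predictor of drug response

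*Protocol article*

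**What the plan says.** The Aims section of the Protocol article lists among the secondary objectives "prediction of treatment response to prednisolone therapy using immune markers (blood samples". The section on laboratory assessments repeats the purpose and makes clear that both arms are sampled: "To investigate immunological biomarkers that predict treatment response to prednisolone therapy, we will collect serum and RNA of all patients".

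The section Power calculation and statistical analysis then fixes the method. The analysis is "Association of clinical outcomes with baseline levels of selected biomarkers in the prednisolone treatment group (i.e., prediction of treatment response", and it "will be assessed using fixed effects analysis of covariance with adjustment for significant covariates". The words in brackets equate the one-arm association with prediction of response.

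Two other biomarker statements stand beside it:

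- A two-arm analysis: "Protein concentrations before and after treatment with prednisolone and placebo will be compared using mixed effects analysis of covariance".
- The sensitivity analyses: "Sensitivity analyses will be conducted by excluding covariates from the analysis of covariance models and, if applicable, including outliers".

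Neither relates a baseline marker to clinical outcome on placebo. The article nowhere mentions a marker-by-treatment term or a parallel placebo-arm analysis.

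**The concern.** To say that a marker predicts response to a drug is to say that the drug's effect differs by marker level. That is a contrast between arms. Within the prednisolone arm alone, the slope of outcome on a baseline marker mixes the course of illness, placebo response and any modification of the drug effect. A marker with the same slope in both arms carries no information about who benefits from prednisolone, yet it would pass the stated test.

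The possibility is not remote on the article's own evidence. The Background reports a study in which "symptom severity was positively associated with the levels of pro-inflammatory markers such as IL-2R, IL-6, and IL-8", so immune markers can track illness severity without any trial drug. The Background also suggests that a pro-inflammatory state may be confined to a subset of patients. The one-arm association is the only stated analysis that links baseline markers to clinical outcome. A prognostic marker presented as a response marker could misdirect the choice of patients in later immune-modulation trials.

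**Working it through.** **The plan's own figures.** The article gives no figure for the biomarker analysis. Its sample size for the primary outcome reproduces: with an effect size of 0.610 and 44 per arm, a two-sided 0.05 t-test has 80.8% power; (1 − 0.48²) × 88 + 1 = 68.72; 68.72 × 1.3 = 89.34, taken up to 90.

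**Inputs from the article.** 90 patients randomised 1:1, so 45 per arm; 30% drop-out, so 45 × 0.7 = 31.5, taken as 31 completers per arm; two-sided alpha 0.05; baseline to 6-week PANSS correlation 0.48; treatment effect 0.61 SD.

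**Assumption.** The partial correlation ρ of the marker with outcome, given baseline, is not in the documents. It is ranged from 0 to 0.5.

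**Model simulated** (4,000 replicates per setting). B is baseline PANSS, M the marker, T treatment, all effects in SD units, with M independent of B:

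Y = 0.48·B + ρ·√(1 − 0.48²)·M − 0.61·T + e, where SD(e) = √(1 − 0.48²)·√(1 − ρ²) and √(1 − 0.48²) = 0.877.

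The marker slope is the same in both arms, so M has no predictive value. Two tests were applied: (a) ANCOVA of Y on B and M in the prednisolone arm only; (b) the T×M term in a model with B, T, M and T×M in both arms.

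| Assumed ρ | (a) one arm, n = 45 | (a) one arm, n = 31 | (b) interaction, 45 per arm | (b) interaction, 31 per arm |
|---|---|---|---|---|
| 0 | 4.8% | 4.6% | 4.8% | 5.2% |
| 0.2 | 25% | 19% | 5.1% | 4.9% |
| 0.3 | 50% | 37% | 5.6% | 4.7% |
| 0.4 | 78% | 61% | 5.5% | 4.3% |
| 0.5 | 94% | 83% | 4.6% | 5.2% |

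**Hand check of (a).** Fisher z, power ≈ Φ(atanh(ρ)·√(n − 3) − 1.96):

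- n = 45, ρ = 0.3: 0.3095 × 6.481 − 1.96 = 0.046, giving 51.8%.
- n = 45, ρ = 0.4: 0.4236 × 6.481 − 1.96 = 0.785, giving 78.4%.
- n = 31, ρ = 0.3: 0.3095 × 5.292 − 1.96 = −0.322, giving 37.4%.
- n = 31, ρ = 0.4: 0.4236 × 5.292 − 1.96 = 0.282, giving 61.1%.

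These agree with the simulation.

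**What the interaction test costs.** Now let the marker act only under prednisolone, with slope ρ × 0.877 there and zero on placebo:

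| Equivalent ρ | (a) n = 45 | (b) 45 per arm | (a) n = 31 | (b) 31 per arm |
|---|---|---|---|---|
| 0.3 | 48% | 28% | 33% | 20% |
| 0.4 | 71% | 44% | 54% | 33% |
| 0.5 | 88% | 62% | 70% | 45% |

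At 0.3 and 45 per arm, the one-arm test is significant in 50% of trials when the marker is purely prognostic and in 48% when it is purely predictive. A significant result therefore does little to tell the two apart. The simulation leaves out the stratification factors and any multiplicity across markers.

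**The case against.** Several objections have force.

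- **The error is conditional.** It arises only if a marker is prognostic; otherwise the one-arm test holds its level. A reader might infer that the trial will name false response markers. The documents support only that it can, because they give no marker-outcome correlation. The Background evidence concerns symptom severity, not outcome at 6 weeks given baseline severity, and need not carry over.
- **The analysis is not empty.** A marker that modifies the drug effect without being prognostic would show up in the prednisolone arm, and the one-arm test is the more sensitive of the two. It is non-specific; it would be too much to say that it cannot bear on the subset hypothesis at all.
- **The placebo samples are not discarded.** They enter the comparison of protein concentrations over time. That comparison shows what the drug does to the marker, not whether the baseline marker changes what the drug does for the patient, so the gap remains.
- **Regression to the mean** is a tempting addition. It depends on whether baseline PANSS is among the adjusting covariates, which the article does not say, so it is not part of the point. The simulation adjusts for baseline and the problem persists.
- **This is a secondary objective in a proof-of-concept trial**, and the interaction test has low power. Both are true. Low power calls for a cautious claim; it does not make a one-arm association an answer to a between-arm question.

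An unseen analysis plan does not dispose of the point, because the article states the one-arm method and its interpretation outright.

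**Conclusion.** The point holds for the response-prediction objective. The stated analysis cannot separate a predictive marker from a prognostic one, so a prognostic marker can be reported as predicting response to prednisolone. Under assumed partial correlations of 0.2 to 0.5, this happens to a purely prognostic marker in about 25% to 94% of trials at 45 per arm and 19% to 83% at 31 completers per arm. The corresponding rate for the interaction test is about 5%. The width of those ranges reflects what the documents leave unknown.

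A reader might infer a threat to the trial's main conclusion. There is none: the primary PANSS comparison, the sample size and the sampling schedule are untouched. This should be fixed, but it is not a condition for the trial's validity.

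**What to change.** Restate the analysis so that it uses both arms. Fit the clinical outcome on its baseline value, treatment, baseline marker, treatment × marker and the stratification factors (country, center, gender). Base any claim of prediction on the interaction estimate with its 95% CI. Report the prednisolone-only association as descriptive, and drop its description as prediction of treatment response.

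The change costs a revised model statement, best made before unblinding. It needs no new samples or visits, since the article already plans that "we will collect serum and RNA of all patients at baseline and 3, 6, and 26 weeks". The price is sensitivity: interaction power is about 28% to 62% at 45 per arm and 20% to 45% at 31 per arm, for assumed effects equivalent to 0.3 to 0.5. The results should therefore be labelled exploratory, and a non-significant interaction should not be read as evidence that no marker matters.
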